#### Secondary outcome measures

Secondary outcome measures include pain, perceived recovery, functional status, patient satisfaction, and disease-specific HR-QOL.

*Pain* will be measured using an 11-point numeric rating scale (NRS) ranging from 0 (no pain) to 10 (worst possible pain) [24]. Patients will be asked to rate their average pain over the last 7 days.

*Perceived recovery* will be measured using the Global Perceived Effect Scale. In clinical practice, measurement of patient-rated recovery often takes the form of the question: to what extent have you improved (or deteriorated) since last time? This type of rating of perceived recovery is a “transition scale” or Global Perceived Effect (GPE) scale, which has been advocated to increase the relevance of information from clinical trials to clinical practice [25]. From the patients’ perspective, the question is intuitively easy to understand and it allows them to rate those aspects of recovery that are most important to them. In the current study, patients will be asked the following question: “to what extend have you recovered since your trauma?” The GPE scale asks the patient to rate, on a 7 item scale, how much their condition has improved or deteriorated since their trauma. Possible answers include 1) completely recovered, 2) much improved, 3) slightly improved, 4) not changed, 5) slightly worsened 6) much worsened and 7) worse than ever [26].

*Functional status* will be measured using the Patient Specific Function Scale (PSFS), a patient specific outcome measure that is intended to complement the findings of generic- or condition-specific measures [27]. Patients will be asked to identify three important activities that they are having difficulty with or are unable to perform. Subsequently, patients are asked to rate their current level of difficulty associated with each activity, on an 11-point numeric rating scale ranging from 0 (“unable to perform activity”) to 10 (“able to perform activity at same level as before injury or problem”). The PSFS is translated and validated for the Dutch population [28].

*Patient satisfaction* will be scored using an 11 point numeric rating scale ranging from 0 (very dissatisfied) to 10 (excellent). Five patient satisfaction components related to the TTCM will be evaluated: 1) total treatment, 2) treatment at the outpatient clinic, 3) treatment in primary care, 4) collaboration between practitioners from the hospital team and 5) collaboration between the hospital team and the primary care physical therapist.

*Disease-specific HR-QOL* will be measured using one of the following disease-specific function scales, appropriate to the patients’ specific injury type (i.e. upper extremity fractures, lower extremity- and hip fractures, vertebral fractures and multi trauma patients):

Patients with fractures of the upper extremity will fill out the Quick Dash score, a short version of the Dash score (Disabilities of the Arm, Shoulder and Hand score) [29]. The Quick Dash score consists of 11 items, measuring physical function and symptoms on a five point scale (1–5 with higher scores indicating greater difficulty) in people with any or multiple musculoskeletal disorders of the upper limb. A validated Dutch version is available and will be used in this study [30].

Physical function in patients with hip fractures or other lower extremity fractures will be measured using the Lower Extremity Functional Scale (LEFS) [31]. The LEFS is a 20-item disease-specific questionnaire developed for measuring physical function in patients with musculoskeletal problems of the lower extremities. Each item is rated on a five point scale (0–4 with higher scores representing higher levels of functioning). The LEFS is frequently used as outcome measure in patients with fractures of the lower extremity [32]. A validated Dutch version of the LEFS will be used in this study [33].

Patients with vertebral fractures will fill out the Roland Morris Disability Score (RMDS) [34]. The RMDS is a disease-specific self-reported questionnaire consisting of 24 items all of which contain two answering categories (yes/no). The RMDS was originally developed for measuring function in patients with chronic low back pain, but is frequently used to evaluate outcome in patients with traumatic vertebral fractures (operated as well as conservatively treated). A validated Dutch version is available and will be used in this study [35].

Physical functioning in multi trauma patients will be assessed using the Groningen Activity Restriction Scale (GARS) [36]. The GARS is an 18 item scale on daily activities, all of which contain four response categories ranging from 1 to 4 representing 1 (being fully independent of other people) to four (being fully dependent of other people). The sum score provides information on the level of difficulty a person experiences in care taking and household activities. Recent research indicates good psychometric properties in a Dutch population of multi trauma patients [37].

#### Costs

Costs will be considered from a societal perspective, meaning that all costs related to the TTCM will be taken into account including intervention, health care, absenteeism, presenteeism and unpaid productivity. Except for intervention costs, costs will be assessed using retrospective cost questionnaires at baseline, 3, 6 and 9 months follow-up. Recall periods of these questionnaires will vary between treatment groups and measurement points in order to cover the complete duration of follow-up. To illustrate, 3-month recall periods will be used for the intervention group at all measurement points, whereas recall periods of 3, 6 and 9 months will be used for baseline/3-month follow-up, 6-month follow-up, and 9-month follow-up for the control group, respectively. All costs will be converted to the same reference year using consumer price indices. Discounting of costs will not be necessary due to the 9-month follow-up period.

*Intervention costs* will consist of all costs related to development and implementation of the TTCM (i.e. personnel costs, material costs, costs of the electronic patient record, educational costs). Intervention costs will be estimated using a bottom-up micro costing approach in which detailed data are collected regarding the TTCM’s units of resource use as well as their respective unit prices [38, 39].

*Health care utilization* will include primary care (e.g. consultations at the general practitioner or physical therapist) and secondary care (e.g. consultations at the outpatient clinic for trauma patients, hospitalization) as well as the use of medication. Dutch standard costs will be used to value health care costs [39]. Use of medication will be valued using the G-standard of the Dutch Society of Pharmacy [40].

*Absenteeism* will be retrospectively assessed using the “PROductivity and DISease Questionnaire” (PRODISQ) asking patients to report their total number of sick leave days [41]. Absenteeism will be valued using age- and gender-specific price weights [39].

*Presenteeism* is defined as reduced productivity while at work and will be assessed using the World Health Organization Health and Work Performance Questionnaire [42]. Presenteeism will be valued using age- and gender-specific price weights [39].

*Unpaid productivity losses* will be assessed by asking patients for how many hours per week they were unable to perform their unpaid activities, such as domestic work, school and voluntary work. Dutch shadow prices will be used to value unpaid productivity [39].

#### Process evaluation

A process evaluation will be performed to explore the extent to which the TTCM was implemented as intended as well as the possible facilitators and barriers associated with its implementation.

The extent to which the TTCM was implemented will be explored by assessing the four process evaluation components of Linnan and Steckler, including reach, dose delivered, dose received, and fidelity [43]. *Reach* is defined as the proportion of the intended target audience that eventually participated in the intervention (i.e. the TTCM). *Dose delivered* is defined as the number of intended units of the intervention provided (e.g. number of scheduled consultations/treatment sessions). *Dose received* is the extent to which trauma patients actively engaged in the intervention (e.g. number of attended consultations/treatment sessions in relation to the number that was scheduled). *Fidelity* is the extent to which the intervention was delivered as planned (i.e. the extent to which the intervention protocol was followed by the various care providers). To explore these four process evaluation components, data will be collected from the intervention group participants’ electronic patient records (e.g. number of secured emails, number of treatments in primary care, was the treatment according the protocol?).

Barriers and facilitators are defined as factors that hampered or enhanced the implementation of the TTCM, respectively [44]. For exploring the barriers and facilitators associated with the implementation of the TTCM, focus groups will be conducted among trauma patients (two focus groups consisting of five patients each), trauma surgeons (one focus group of six trauma surgeons), hospital based physical therapists (one focus group of five hospital based physical therapists), and primary care network physical therapists (two focus groups consisting of five primary care network physical therapists). Focus groups will be conducted at a time and location convenient to the participants. Prior to the focus groups, participants will be assured of confidentiality and will be asked to provide informed consent. The focus groups will be guided by two researchers, familiar with the TTCM, but not involved as care provider in the TTCM. During the focus groups, three round table discussions will be held; the first will be aimed at identifying possible facilitators, the second will be aimed at identifying possible barriers and the third round will be aimed at complementing and validating the barriers and facilitators identified in round one and two. During all round table discussions, a topic list will be used as a guide, but participants are allowed to discuss other topics that they consider to be of importance as well. All focus groups will be audiotaped and transcribed verbatim.

### Data analysis

#### Descriptive statistics

Descriptive statistics will be used to compare baseline characteristics between control- and intervention group participants and participants with complete and incomplete data.

#### Handling missing data

Missing data are assumed to be at random and will be imputed using Fully Conditional Specification and Predictive Mean Matching [45]. An imputation model will be constructed, including variables related to the “missingness” of data, variables that predict the outcomes, and all available midpoint and follow-up cost and effect measure values. The number of imputed data sets will be determined based on the number of participants with complete cost and effect measure values [46]. All of the imputed datasets will be analysed separately as specified below. Pooled estimates were subsequently calculated using Rubin’s rules [46].

#### Clinical effectiveness

The clinical effectiveness analyses will consist of two parts. First, the TTCMs’ effectiveness in terms of HR-QOL, pain, perceived recovery, functional status and patient satisfaction compared with usual care will be explored at 3, 6 and 9 months follow-up using regression analyses. The four clusters of control patients (i.e. time after their first consultation at the outpatient clinic for trauma patients respectively 0, 3, 6 and 9 months) will be compared with the patients in the intervention group at the corresponding time points. Second, the recovery pattern of patients in of the intervention group will be studied using longitudinal data analysis in terms of HR-QOL, pain, perceived recovery, functional status and patient satisfaction during the 9 month follow-up period (and while receiving the TTCM). All of the aforementioned analyses will be corrected for confounders if necessary (e.g. age, gender, level of education). Confounding will be checked by adding the potential confounding variable to the crude models, and will subsequently be considered to be present if the regression coefficient changes by 10% or more. All of the clinical effectiveness analyses will be performed in SPSS, using a level of significance of *p* < 0.05.

#### Economic evaluation

The economic evaluation will be performed from the societal perspective, meaning that all costs and consequences related to the intervention will be taken into account, irrespective of who pays or benefits. The mean difference in total costs between the intervention and control group will be compared to the corresponding mean difference in effects. For this, cost and effect differences will be estimated using seemingly unrelated regression analyses in order to correct for their possible correlation. To deal with the highly skewed nature of cost data, 95%CIs around the differences in costs will be estimated using the Bias Corrected and Accelerated Bootstrap method, with 5000 replications. Incremental Cost Effectiveness Ratios (ICERs) will be calculated by dividing the differences in costs by those in effects. To graphically illustrate the uncertainty surrounding the ICERs, bootstrapped incremental cost-effect pairs will be plotted on cost-effectiveness planes [47]. A summary measure of the joint uncertainty of costs and effects will be presented using cost-effectiveness acceptability curves, indicating the probability of an intervention being cost-effective in comparison with the control condition for a range of willingness-to-pay values (i.e. the maximum amount of money decision-makers are willing to pay per unit of effect gained) [48]. To test the robustness of the results, various sensitivity analyses will be performed [49]. All of the economic evaluation analyses will be performed in STATA, using a level of significance of *p* < 0.05.

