The majority of trauma patients have one or more fractures due to their trauma, sometimes in combination with organ system injuries. Fractures of the lower extremities in particular have a major impact on functional status and health-related quality of life (HR-QOL) [5, 6]. Moreover, the economic burden of trauma to society is extensive due to the associated high *direct* as well as *indirect* costs (e.g. absenteeism costs). To illustrate, the total costs per patient with an operatively treated vertebral fracture is estimated to be €66.000, of which the majority (i.e. €47.000) is due to increased absenteeism [7]. Due to the major impact of trauma on mortality, morbidity, and (societal) costs, there has been increased interest in the organization of trauma care over the last three decades. In the literature it is frequently mentioned that trauma care is a chain of services, consisting of pre-hospital care, resuscitation and in-hospital care. During the last two decades, an improved organization of *pre-hospital* and *in-hospital* care by developing specialized trauma centers using Advanced Trauma Life Support (ATLS®) guidelines, has led to a 15–25% decrease in mortality of severe trauma patients [8–11]. Since mortality has decreased significantly due to this re-organization of trauma care, it has been suggested that the focus of trauma care should shift to *improving quality of life and outcome*, rather than on survival of trauma patients, because further improvements in survival rates are likely to be small [8, 11]. To improve quality of life and outcome among trauma patients, more attention for optimizing the rehabilitation phase is crucial. Even though numerous studies investigated the outcome of trauma patients, none of these studies focused on the *organization* and *content* of post-clinical trauma care. It is recognized that serious gaps exist between patients’ transition from acute care to rehabilitation and their return to society [12–14]. Therefore the limited focus on post-clinical trauma care is remarkable. Recently the American Trauma Society developed a post-clinical psychological support program, including self-management and peer support to improve the trauma patients’ psychosocial outcomes [15]. Nonetheless, there is limited attention for optimizing the organization of the post-clinical *physical* rehabilitation of trauma patients in primary care, which may have led to an inefficient and/or suboptimal rehabilitation process. After being discharged from a hospital, the majority of Dutch trauma patients rehabilitates in the primary care setting (i.e. treatment by a primary care physical therapist). In contrast to secondary and tertiary care, however, guidelines and protocols, as well as an interdisciplinary coordination, are lacking in primary care.

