### Population

A total of 300 trauma patients will be included in the study. Both operatively and non-operatively treated patients will be included, irrespective of whether or not they were admitted to the hospital. In order to be eligible for inclusion, trauma patients have to meet the following inclusion criteria: having at least one traumatic fracture, being aged >18 years, and being able to fill out online questionnaires. In both the intervention- and control group, the duration between the patients’ actual trauma and their first consultation at the outpatient clinic for trauma patients can vary, depending on the treatment that was selected at the emergency department (i.e. admitted to hospital or sent home). Patients will be excluded if they have red flags (i.e. traumatic brain injury, pathological fractures, and/or cognitive limitations), if they do not speak Dutch, if their rehabilitation process takes place in a tertiary care facility, and/or when patients live outside the catchment area of the VUmc.

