### Outcome assessment

An overview of all outcome measurements is provided in Table 1.

**Table 1 Tab1:** Overview of all outcome measurements

Outcome	Measurement Instrument	Short term	Items	Itemscore	Interpretation
General ﻿HR-QOL	EQ-5D	EQ-5D	5	1–3	higher score: better health
Pain	Numeric Pain Rating Scale	NPRS	1	0–10	higher score: more pain
Perceived recovery	Global Perceived Effect	GPE	2	1–7	higher score: less recovery
Functional status	Patient Specific Function Scale	PSFS	3	100 mm VAS	higher score: less function
Patient satisfaction	Numeric Rating Scale	NRS	5	0–10	higher score: more satisfaction
Disease specific HR-QOL (upper extremity)	Quick Dash score	Q-DASH	11	1–5	sumscore 0–100, higher score: less function
Disease specific HR-QOL (lower extremity)	Lower Extremity Functional Scale	LEFS	20	0–4	sumscore 0–80, higher score: better function
Disease specific HR-QOL (vertebral fractures)	Roland Morris Disability Score	RMDS	24	yes/no	sumscore 0–24, higher score: more disability
Disease specific HR-QOL (multi trauma patients)	Groningen Activity Restriction Scale	GARS	18	1–4	sumscore 18–72, higher score: more restrictions
Healthcare utilization	Retrospective Cost Questionnaires				costs in Euro’s
Absenteeism	PROductivity and DISease Questionnaire	PRODISQ	1		total number of sick leave days
Presenteeism	WHO Health and Work Performance Questionnaire (NRS)	WHO-HPQ	1	0–10	higher score: better performance at work
Unpaid productivity loss			1		hours per week unable to perform unpaid activities

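### The societal perspective is defined as all costs, but none of the cost categories described covers informal care received from family or others

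*Protocol article*

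**What the plan says.** The Economic evaluation section adopts the societal perspective, "meaning that all costs and consequences related to the intervention will be taken into account, irrespective of who pays or benefits". The Costs section says the same and names the components: "meaning that all costs related to the TTCM will be taken into account including intervention, health care, absenteeism, presenteeism and unpaid productivity". The Methods part of the Abstract and the second research question in the Background name the same five components.

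The Costs section then takes the components one at a time. Health care utilization "will include primary care (e.g. consultations at the general practitioner or physical therapist) and secondary care", and also medication. Unpaid productivity loss "will be assessed by asking patients for how many hours per week they were unable to perform their unpaid activities", and it is valued at Dutch shadow prices. Everything except intervention costs comes from retrospective questionnaires.

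Table 1 is introduced with the words "An overview of all outcome measurements is provided in Table 1". Its cost rows are health care utilization, absenteeism, presenteeism and unpaid productivity loss. No row concerns help received from others.

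**The concern.** The definition turns on costs counting whoever bears them. Time given by a partner, relative or friend is a clear example of a cost that falls outside the health system, the employer and the patient. It is also a resource the TTCM could change: according to the Discussion, the model aims to improve functional outcome, and a patient who functions better may need less help at home.

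If that time is not collected, it is absent from total costs, from the ICER, from the cost-effectiveness planes and from the acceptability curves. The bootstrap cannot make this good, because it resamples only costs that were recorded. A reader who takes the stated definition at face value would believe that helpers' time had been counted.

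**Working it through.** The protocol states no figure on this point, so there is nothing to reproduce. The check sets the definition beside the categories described.

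1. **Definition.** Economic evaluation and Costs: all costs, with no payer left out.

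2. **Categories, and whether each could hold informal care:**
   - Intervention costs: personnel, materials, the electronic patient record and education for the TTCM. No.
   - Health care utilization: primary care, secondary care and medication, valued with Dutch standard costs and a pharmacy price list. These are formal services. No.
   - Absenteeism: the patient's own sick leave days. No.
   - Presenteeism: the patient's own reduced performance at work. No.
   - Unpaid productivity: hours per week in which the patient could not do his or her own unpaid activities. This is the patient's loss, not the time a helper gives. No.

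3. **Table 1.** It has no row for help received. The row for health care utilization names only retrospective cost questionnaires and does not list their items.

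4. **Relevance in this population.** Patients have at least one fracture, and the Abstract describes them as discharged home. For multi trauma patients the protocol uses the GARS, whose response categories run from full independence of other people to full dependence on them. Its sum score describes "the level of difficulty a person experiences in care taking and household activities". The GARS is not given to the other injury groups and does not record hours of help. It shows that dependence on others is anticipated in some patients, and nothing about its amount.

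5. **What the omission does to the estimate.** Let Δh be the difference between groups in mean hours of informal care per patient over follow-up (intervention minus control), and p the price per hour. Then:
   - full cost difference = measured cost difference + p × Δh
   - full ICER = measured ICER + (p × Δh) / ΔE, where ΔE is the difference in effect.

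   Only the difference Δh matters, not the total hours of help per patient. The documents give neither Δh nor p. If the TTCM reduces the need for help, Δh is negative and the measured cost difference is too high. If it increases the need, the reverse holds. The sign cannot be settled from the text.

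**The case against.** The strongest defence is that the lists are open. The five components follow the word *including*, health care is illustrated by examples, and the article condenses a fuller protocol whose questionnaire is not shown. An item on informal care could exist there. Nor is Table 1 a complete cost inventory: it has no row for intervention costs or for medication, both of which the Costs section says will be counted. This lowers certainty but does not remove the mismatch. The same five components appear in the Abstract, the research questions and the Costs section, each is then described separately, and none can absorb a helper's time. If the item exists, one added sentence settles the point.

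A second defence is that some helper time is already priced indirectly: when a relative takes over the patient's housework, the patient's lost unpaid hours may capture the same task. That holds for domestic tasks, but not for personal care and other help the patient would not otherwise have needed.

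A reader might go further and infer two things that the documents do not support. The first is that tertiary rehabilitation is also wrongly left out. The Population section excludes patients "if their rehabilitation process takes place in a tertiary care facility", in both groups, so its absence from the cost list follows from the eligible population. Nothing in the document shows transfers after inclusion. Counting tertiary days would also be lopsided. Controls in the 3-, 6- and 9-month clusters are identified from records and screened after that time has passed, so such patients would already have been removed from those clusters, and the cost would fall almost only on the intervention group. The second is that the societal perspective is not delivered at all. That is too strong, because absenteeism, presenteeism and unpaid work are counted well beyond health care costs.

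**Conclusion.** The point holds for informal care only. The stated definition is wider than the cost categories described, and help from family or others is the gap. The cost difference and the ICER are therefore not fully societal as the protocol defines the term. The size and direction of the effect on either cannot be derived from the documents, and any amount in euros would rest wholly on assumed hours and prices.

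The conclusion assumes that the cost questionnaire follows the categories described in the Costs section, since its items are not listed. It is a matter worth correcting, because the remedy is small and the claim is prominent. It does not invalidate the economic evaluation.

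**What to change.** Add one item to the cost questionnaire in both groups, asking how many hours per week of unpaid help the patient received from family or others. Use the recall periods already set for each group and measurement point. Value the hours at the shadow price already used for unpaid work and include the result in total costs. Word the item so that housework taken over from the patient is not counted both here and as the patient's lost unpaid hours.

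If the questionnaires can no longer be changed, narrow the all-costs wording in the Abstract (Methods), the Costs section and the Economic evaluation section to the categories measured, limit the conclusion to those categories, and state the omission of informal care as a limitation. If the item is already in the questionnaire, name it in the Costs section and in Table 1.

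The cost is slight extra respondent burden and one more valuation step, or else a narrower claim.
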